### Aims of the study

The FatiGo trial is designed to address the following primary objectives:

 1. To assess the differences in treatment effect (change between baseline and
6-month follow-up in fatigue severity and quality of life) in patients with CFS
between individual multidisciplinary rehabilitation treatment (MRT) and
individual cognitive behavioural therapy (CBT).

 2. To assess the differences in long-term treatment effect (change between
baseline and 12-month follow-up in fatigue severity and quality of life) in
patients with CFS between the two treatments.

 3. To assess the difference in cost-effectiveness and cost-utility between MRT
and CBT from both a health care and societal perspective at 12-month
follow-up.

 4. To assess the differences in treatment effect in psychological symptoms,
self-efficacy, causal attributions, present-centred attention-awareness, impact
of disease on physical and emotional functioning, self-rated improvement and
life satisfaction between MRT and CBT (at 6- and 12-month follow-up).

The secondary objectives of this trial are:

 1. To assess the influence of patients treatment expectancy and credibility on
the effectiveness of treatment.

 2. To assess what baseline factors (other than the assigned treatment) predict a
change in fatigue and increase in quality of life in all participants.

 3. To evaluate whether changes in self-efficacy, changes in causal attributions
and/ or changes in present-centred attention-awareness (at baseline, 6 and 14
weeks after start of treatment) mediate changes in fatigue severity and changes
in quality of life after treatment.

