#### Mediation

In order to understand how treatment works, mediation analyses are performed.
Two studies on mediation could not confirm the mediating role of physical
activity in reducing fatigue in CFS. Moss-Morris (2005) [21] investigated physical activity as a
mediator in the treatment effect of GET and Wiborg (2010) [65] in CBT. Since physical activity does
not mediate the outcome, other parameters have to be responsible for a
decrease of fatigue during therapy. In the model of Vercoulen et al.
[14], somatic attributions,
focussing on pain and fatigue, and low self-efficacy contribute to the
perpetuating of CFS complaints. Patients with CFS feel helpless and
surrendered to their complaints, making it difficult to change their
situation. During therapy patients learn to change cognitions into more
helpful cognitions, which increases self-efficacy. They learn to accept
their situation in the present, making choices based on helpful cognitions
and bodily symptoms other than pain and fatigue, and learn to focus on
getting better instead of focussing on complaints and somatic attributions.
Our hypothesis is that by increasing self-efficacy, decreasing somatic
attributions and increasing the present-centred attention-awareness during
activities first, behavioural changes can be made based upon these changes
and eventually the severity of fatigue will decrease.

There are no studies that we are aware of that determine the mediating role
of self-efficacy, somatic attributions and present-centred
attention-awareness. Mediation will be investigated by the three-step method
described by Baron and Kenny [66].
Before treatment (T1), 6 and 14 weeks after start of treatment (T2, T3),
CIS, SE28, CAL and MAAS are filled in by the patient in order to analyse
mediation at different moments during treatment phase.

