#### Mediation analyses

In the mediation analysis, we investigate whether self-efficacy, somatic
attributions and/or present-centred attention-awareness intervenes in the
relationship between treatment and outcome. Multiple regressions are used to
explore which factors mediate the outcome. Mediation is suggested when the
change in the putative mediating factors is significantly related to
treatment as the independent variable, outcome is significantly related to
treatment as the independent variable, and finally, the relationship between
outcome and treatment decreases (or goes to zero) when the change in the
mediation factor is entered into the equation [66].

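### The mediation rule accepts any fall in the treatment coefficient, untested, and requires a significant total effect, so it can suggest false mediators and miss real ones

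*Protocol article*

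**What the plan says.** Mediation is the third secondary objective under Aims of the study: "3. To evaluate whether changes in self-efficacy, changes in causal attributions" and changes in present-centred attention-awareness account for changes in fatigue severity and quality of life. The Mediation paragraph under Outcome measures names the approach: "Mediation will be investigated by the three-step method", with a citation, and schedules the mediators at baseline and at 6 and 14 weeks.

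The Mediation analyses section then gives the decision rule. It opens "Mediation is suggested when the" and lists three conditions:

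1. the "change in the putative mediating factors is significantly related to" treatment;
2. the outcome is also significantly related to treatment;
3. the relationship between "outcome and treatment decreases (or goes to zero) when the change in the" mediating factor is entered into the equation.

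The first two conditions need significance. The third needs only a decrease; no test, interval or minimum size is attached. A significant relation between mediator and outcome, given treatment, is not among the conditions. The language is tentative: regressions are used to "explore which factors mediate the outcome".

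**The concern.** A mediated effect needs two links: treatment must move the mediator, and the mediator must move the outcome. The rule tests the first and replaces the second with the direction of change in a coefficient. A mediator unrelated to outcome still shifts the treatment coefficient a little through sampling error, and it does so downwards about as often as upwards.

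The exposed situation is the one the trial expects. Hypotheses on the primary objectives predicts that MRT beats CBT on fatigue and quality of life, and also on self-efficacy, non-physical attributions and attention-awareness. If those predictions are right, conditions 1 and 2 tend to pass and condition 3 decides, separately for each of three candidate mediators.

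The second condition errs the other way. Both arms are active and share three elements (The interventions), so the total difference may be small. If it is not significant, the rule cannot support any mediator, however clear the two links are, and secondary objective 3 goes unanswered.

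**Working it through.** **Inputs from the protocol.** Sample size gives 48 evaluable patients per arm, alpha 0.05, power 0.80 and a difference of 3.0 CIS points; 120 are recruited with 25% dropout expected. If exactly 25% drop out, 120 × 0.75 / 2 = 45 per arm remain.

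**The plan's own figure.** The mediation section states none. The 48 per arm reproduces two-sided with an SD of 5.2, inside the stated 3.9 to 5.9 (power 0.807). The standardised difference detectable with 80% power is (1.960 + 0.842) × √(2/48) = 0.57 SD, used below as a value near the design effect.

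**Assumptions.** The protocol gives no path sizes. In residual-SD units let a be treatment to mediator, b mediator to outcome given treatment, and c′ the direct effect; the total effect is c = c′ + a·b. Conditions 1 and 2 are taken at two-sided 0.05, and condition 3 as |c′ estimate| < |c estimate|. The model is linear and normal with no mediator-outcome confounding. The comparator is a joint test requiring both a and b to be significant. Each 48-per-arm scenario used 40,000 simulated trials, and each 45-per-arm scenario 8,000.

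**False positives (b = 0).** The chance of meeting the rule is P(conditions 1 and 2) × P(condition 3, given both).

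| Per arm | a | c | P(1 and 2) | P(3 given 1, 2) | Written rule | Joint test |
|---|---|---|---|---|---|---|
| 48 | 0.57 | 0.50 | 0.533 | 0.501 | 27% | 3.9% |
| 48 | 0.57 | 0.57 | 0.629 | 0.499 | 31% | 3.9% |
| 48 | 1.0 | 0.57 | 0.792 | 0.500 | 40% | 5.1% |
| 48 | 1.0 | 1.0 | 0.996 | 0.494 | 49% | 5.0% |
| 48 | 0 | 0.57 | 0.038 | 0.499 | 1.9% | 0.3% |
| 48 | 0.57 | 0 | 0.038 | 0.512 | 2.0% | 3.9% |

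For example, 0.629 × 0.499 = 0.314. At 45 per arm, a = 0.6 with c = 0.5 or 0.6 gives 25% and 32% for the rule, against about 4%. A percentile bootstrap interval for a·b in the scenarios where treatment moves both variables flags about 3 to 7%.

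**Missed mediators (b = 0.5).** Here condition 2 is the obstacle. With a = 0.57, c′ = 0 and 48 per arm, c = 0.57 × 0.5 ≈ 0.29. The outcome SD within arm is √(1 + 0.5²) = 1.118, so the standard error of c is 1.118 × √(2/48) = 0.228. The ratio is 0.286 / 0.228 = 1.25, and Φ(1.25 − 1.96) ≈ 0.24, close to the simulated 0.236 for condition 2.

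| Per arm | a | c′ | Total c | Written rule | Joint test |
|---|---|---|---|---|---|
| 48 | 0.57 | 0 | 0.29 | 22% | 79% |
| 48 | 0.8 | 0 | 0.40 | 40% | 97% |
| 45 | 0.6 | 0 | 0.30 | 22% | 80% |
| 45 | 0.6 | −0.3 | 0 | 2% | 80% |
| 48 | 0.57 | 0.28 | 0.57 | 60% | 79% |

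For complete mediation with a total of 0.3 SD, a run with the bootstrap interval gave 81%, against 23% for the rule.

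**Both faults need repair.** Adding a significant b path to the written rule cuts false positives to 1.6 to 2.4% in the scenarios with b = 0 and both treatment effects at least 0.57 SD. Detection stays at 22% and 40% in the first two complete-mediation rows.

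**A limit common to both.** With a residual mediator-outcome correlation of 0.3, b = 0 and a = c′ = 0.57, the written rule flags 65% and the joint test 67%.

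**The case against.** Five points can be made for the plan.

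- **Status.** This is an exploratory secondary analysis that says mediation is suggested, not shown, and no primary claim depends on it. That stands and limits the weight of the point. It does not make the rule informative, and the Discussion lists mediators among the results to be provided.
- **Condensed article.** Estimates and intervals may be left to an analysis plan that is not shown, and the cited method is not at hand. This would answer a complaint about missing detail. Here the decision rule itself is written out, and following it as written gives the results above.
- **The mediator-outcome path.** A reader might infer that it is never estimated. The text does not support that: entering mediator change into the outcome regression yields its coefficient. The fault is that no condition depends on it.
- **The total effect.** Asking whether a factor intervenes between treatment and outcome presupposes a relation between them, and the trial is powered for 0.5 SD. The largest power losses come from totals below that. This stands in part: near the design effect the gap is 60% against 79%. But no significant difference between the arms is a plausible outcome with two active treatments.
- **Invented path sizes.** They are assumptions. The coin toss at condition 3 does not depend on their exact values once treatment moves both variables; the overall percentages do.

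**Conclusion.** The point holds as a recommendation, not as a fault in the primary analysis. When treatment affects both mediator and outcome but the mediator does not affect outcome, the written rule suggests mediation in roughly 25 to 50% of trials (45 to 48 per arm, assumed effects 0.5 to 1.0 SD), against about 3 to 7% for a test of the indirect effect. For real mediators with the assumed paths (about 0.6 SD, slope 0.5), detection is about 23% against 81% at a total of 0.3 SD, 2% against 80% at a total of zero, and 60% against 79% near the design value.

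A reader might infer that the rule is wrong half the time for any null mediator. That does not follow. One half is the chance of passing condition 3 once conditions 1 and 2 are met, and the plan requires all three. The overall error approaches one half only when both treatment effects are almost certain to be significant, and it is about 2% when treatment does not move the mediator. All comparator figures assume no unmeasured mediator-outcome confounding.

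**What to change.** In the Mediation and Mediation analyses sections, replace the three-step criterion with the following:

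- **Estimate:** the indirect effect for each candidate mediator, as the treatment-to-mediator coefficient times the mediator-to-outcome coefficient adjusted for treatment. Both models also adjust for baseline mediator, baseline outcome and centre.
- **Uncertainty:** a percentile bootstrap 95% confidence interval. Mediation is supported when it excludes zero.
- **No gate:** a significant total effect is not required.
- **Timing:** the mediators already planned at 6 and 14 weeks, with the later outcome.
- **Reporting:** label the analysis exploratory and state that it assumes no unmeasured mediator-outcome confounding, which neither the written rule nor this replacement removes.

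The cost is revised wording and a little programming. Economic analyses already plans bootstrap percentile intervals for costs, and no new data are needed.

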#### Participant non-adherence with treatment

Participant non-adherence with treatment will be measured both by recording
attendance and by therapist ratings of adherence to therapy.

#### Trial management and oversight

The day-to-day management of the trial is carried out by the principal
investigator, [name], in consultation with other members
of the trial team and the research assistants. Every rehabilitation centre
has one or two research assistants.

## Discussion

Treatment facilities for patients with CFS in multidisciplinary rehabilitation
settings are rare, because most health insurance companies and rehabilitation
centres are not convinced of the benefit of MRT for this group. MRT in this form is
unique and has never been investigated in a multicentre RCT. The results of the
FatiGo trial will provide information on the effects of CBT and MRT, mediators of
the outcome, cost-effectiveness, cost-utility and the influence of treatment
expectancy and credibility on the effectiveness of both treatments in patients with
CFS.

### Trial status

At the time of the first submission of the manuscript, data collection was
ongoing. Currently the data collection has been completed. The data will be
analysed from May until October 2012. Results of the trial will be available in
November 2012.
